## 9. Statistical Analysis

### 9.1. Primary Endpoint Analysis

To evaluate the primary endpoint of the study—defined as a ≥10% improvement in VO_2_max at 8 weeks—paired comparisons between baseline and post-intervention values will be performed using a paired t-test for normally distributed data [36,37,38]. For non-normally distributed data, the Wilcoxon Signed-Rank test will be applied. Additionally, the proportion of patients achieving the predefined VO_2_max improvement threshold will be analyzed using logistic regression, with “Rehabilitation Type (Telerehabilitation vs. Standard)” as the main predictor. The model will be adjusted for clinically relevant covariates identified through baseline comparisons using ANOVA or chi-square tests. Odds ratios and 90% confidence intervals will be reported.

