## Abstract

**Background:** Despite strong guideline recommendations, participation in cardiac rehabilitation (CR) among patients with chronic heart failure (CHF) remains low due to logistical, geographical, and psychosocial barriers. Telerehabilitation may help overcome these limitations by offering remote, structured exercise programs supported by digital technologies. **Objective:** The TELEREHAB-HF study aims to evaluate the efficacy of an 8-week, home-based cardiac telerehabilitation program compared to standard in-person rehabilitation in patients with CHF. **Methods:** This is a prospective, controlled cohort study involving 220 adult patients with CHF (NYHA class I–III) clinically stable and on optimized therapy. Participants are assigned to either a telerehabilitation group (remote CR via a digital platform with wearable sensors and real-time physiotherapist supervision) or a standard in-person rehabilitation group. The primary outcome is the change in peak oxygen uptake (VO_2_max) at 8 weeks. Secondary outcomes include quality of life, functional performance, biochemical and echocardiographic parameters, and cognitive function, assessed at baseline and at 4, 8, 16, and 24 weeks. **Expected Results**: We hypothesize that telerehabilitation will be non-inferior to standard CR in improving functional capacity and secondary outcomes, with additional benefits in accessibility and adherence. Data from remote monitoring may also support a translational “rehabilomics” approach to exploring exercise-induced biomarker changes. **Conclusions:** This study seeks to assess the clinical effectiveness, safety, and feasibility of a home-based telerehabilitation model for CHF, with the goal of informing future strategies for broader implementation and personalized rehabilitation. Trial Registration: ClinicalTrials.gov Identifier: NCT07023536

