This protocol describes a prospective, controlled study designed to evaluate the efficacy of an 8-week home-based cardiac telerehabilitation program, supported by real-time remote monitoring technologies, in patients with CHF. The primary objective is to assess improvements in exercise capacity, measured via peak oxygen uptake (VO_2_max), compared to standard in-hospital rehabilitation. Secondary outcomes will include biochemical, functional, and QoL measures.

In addition, the study adopts a translational and “rehabilomic” perspective, aiming to explore the role of exercise as a modulator of specific molecular pathways involved in heart failure [19,20]. By identifying circulating biomarkers that are both pathophysiologically relevant and potentially responsive to physical training, the study seeks to contribute to the development of personalized rehabilitation strategies and a deeper molecular characterization of CHF patients [21].

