## 5. Remote Group (TELEREHABILITATION—YES)

Sessions are delivered synchronously at the patient’s home via a digital telerehabilitation platform (Khymeia VRRS Home System), enabling real-time audiovisual interaction with the physiotherapist. Patients are equipped with a home-based kit including a tablet, wearable sensors (K-RING, K-SENSOR), a spirometer (K-SPIRO), and a health monitor capable of recording ECG, HR, SpO_2_, and BP. The sensors adopted in the TELEREHAB-HF protocol were selected to ensure clinically relevant, real-time, and multidimensional monitoring of patients during home-based cardiac rehabilitation. These sensors were preferred over alternative solutions (e.g., consumer-grade smartwatches, standalone wearable ECG monitors, or optical motion capture systems) due to their medical-grade certification, full integration with the Khymeia VRRS platform, and ability to support both synchronous feedback and asynchronous data collection. Their interoperability, reliability, and user-friendliness in non-clinical environments make them particularly suitable for patients with chronic cardiovascular conditions undergoing home-based telerehabilitation.

All data are transmitted and stored securely in compliance with data protection regulations. Movement execution is monitored through inertial sensors, and real-time feedback is provided to ensure exercise accuracy. Borg and RPE scales are administered online during sessions.

In both groups, outcome measures (Anthropometric measures, CPET, 6MWT, SPPB, echocardiography, QoL questionnaires, laboratory tests, and MMSE) will be collected at baseline (T = 0), during the intervention (T = 1, at 4 weeks), post-intervention (T = 2, at 8 weeks), and during follow-up at 16 (T = 3) and 24 weeks (T = 4). Patients in the telerehabilitation group experiencing clinical or technical issues may transition to in-person sessions to ensure therapeutic continuity.

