## 8. Outcomes

Both groups will undergo standardized assessments at baseline (T0), mid-treatment (4 weeks, T1), post-treatment (8 weeks, T2), and at follow-up timepoints (16 weeks, T3; 24 weeks, T4). Evaluations will include cardiopulmonary functional performance, echocardiographic measurements, biochemical markers, cognitive function, and QoL (Table 3).

The primary outcome of the study is the improvement in functional capacity, assessed as a ≥10% increase in VO_2_max, measured via CPET at 8 weeks (T2).

Secondary outcomes include:QoL: Assessed using the KCCQ-12 and SF-36 at each timepoint.Biochemical parameters: Changes in BNP, NT-proBNP, creatinine, eGFR, serum electrolytes (sodium, potassium, chloride), glucose, and lipid profile.Functional assessments: Performance on the 6MWT and SPPB.Cognitive status: Assessed with the MMSE.Echocardiographic parameters: Left ventricular ejection fraction (LVEF), diastolic function indices (E/A—Ratio of early E to late A ventricular filling velocities; E/e’—Ratio of early transmitral flow velocity to early diastolic mitral annular velocity), and right ventricular function (TAPSE—Tricuspid Annular Plane Systolic Excursion, RVs’—Right Ventricular Systolic Velocity).Adverse events: Monitoring of any complications related to training or telemonitoring (e.g., hypotension, arrhythmias, device issues).

These outcome measures will allow for a comprehensive and longitudinal evaluation of the effects of both in-person and telehealth cardiac rehabilitation on patients with chronic heart failure.

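### The first-named primary analysis is a within-patient paired test that compares no arms and ignores the 10% threshold, and no rule ranks it against the between-arm logistic model

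*Protocol article*

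**What the plan says.** The question is comparative. The Abstract aims to "evaluate the efficacy of an 8-week, home-based cardiac telerehabilitation program compared to standard in-person rehabilitation in patients with CHF", Section 1 repeats that exercise capacity is assessed "compared to standard in-hospital rehabilitation", and the Abstract adds: "We hypothesize that telerehabilitation will be non-inferior to standard CR in improving functional capacity and secondary outcomes". Section 9.3 sizes the trial on an increase in the intervention arm relative to control. Section 8 and Table 3 define the primary outcome as a VO2max gain of at least 10% at week 8.

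Section 9.1 then evaluates that endpoint in two ways. First: "paired comparisons between baseline and post-intervention values will be performed using a paired t-test for normally distributed data", with the Wilcoxon signed-rank test if the data are not normal. Second: "Additionally, the proportion of patients achieving the predefined VO_2_max improvement threshold will be analyzed using logistic regression", with rehabilitation type as the main predictor, adjustment for covariates picked from baseline comparisons, and odds ratios with 90% intervals. The section does not say which of the two is the primary test. Section 9.2 applies a two-sided 0.05 threshold to all final analyses.

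**The concern.** A paired test of baseline against week 8 asks whether the mean change differs from zero. It does not ask whether remote delivery does as well as in-person delivery, or whether anyone gained 10%. It also cannot separate the effect of training from time, familiarity with the test or regression to the mean.

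This matters here because Sections 2 and 3 give both arms the same structure and intensity of exercise, so improvement is expected in both. A significant paired result is then likely whether telerehabilitation is better than, equal to or worse than standard rehabilitation. Since that test is named first for the primary endpoint and no hierarchy is stated, a before-after result could be reported as the trial's primary success even where the arm comparison points the other way.

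**Working it through.** **The plan's own figure.** Section 9.3 gives 200 patients for 90% power at two-sided 0.05, without an SD, responder rates, an allocation ratio or a named test, so 200 cannot be derived from the stated inputs. Back-solving for two means at 100 per arm gives d = √(2/100) × (1.960 + 1.282) = 0.458. For a 10-point difference in percentage change, that is an SD of 10/0.458 = 21.8 points. I use this as one assumed SD and 15 points as a more favourable one.

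**Further assumptions.** 100 analysed per arm, normally distributed changes, and the paired test run within the remote arm (Section 9.1 does not say whether it is run by arm or pooled). Mean gains and the mL/kg/min SDs are also assumed.

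**Smallest observed gain that is significant in the paired test, n = 100:** 1.984 × SD/√100.
- SD 15 points: 1.984 × 1.5 = 3.0%.
- SD 21.8 points: 1.984 × 2.18 = 4.3%.

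Both are well below 10%, and neither depends on the other arm.

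**Power of each test.** Non-central t with noncentrality gain/(SD/√100) for the paired test and difference/(SD × √(2/100)) for the between-arm test on mean change. The joint probability of a significant paired test and a significantly worse remote arm was simulated.

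| Gain, remote vs standard | SD | Paired: noncentrality, power | Remote significantly worse: noncentrality, power | Both |
|---|---|---|---|---|
| 0.75 vs 1.5 mL/kg/min | 3 | 2.50, 0.70 | 1.77, 0.42 | 0.19 |
| 0.75 vs 1.5 mL/kg/min | 2.5 | 3.00, 0.84 | 2.12, 0.56 | 0.42 |
| 6% vs 15% | 21.8 points | 2.75, 0.78 | 2.92, 0.83 | 0.61 |
| 6% vs 15% | 15 points | 4.00, 0.98 | 4.24, 0.99 | 0.97 |

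The joint figure is below the product of the two powers (first row: 0.70 × 0.42 = 0.29, against 0.19). The remote-arm mean enters both tests, and a high value helps the first and hurts the second.

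**If the paired test pools both arms (n = 200),** a true mean gain of only 5% is significant with power 0.90 (SD 21.8) to 0.997 (SD 15).

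**What the planned responder comparison would show.** The responder rate is 1 − Φ((10 − mean)/SD).
- 6% vs 15%, SD 15: 39.5% vs 63.1%, odds ratio 0.38, power 0.92 (unadjusted two-proportion test).
- 6% vs 15%, SD 21.8: 42.7% vs 59.1%, odds ratio 0.52, power 0.64.

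**The case against.** The best defence is that the right analysis is already there. Section 9.1 plans an adjusted logistic model on the exact 10% endpoint with arm as the main predictor, Section 9.3 is worded as a contrast with control, and Section 2 mentions propensity score methods. A reader might infer from the paired test that the arms are never compared. The documents do not support that, and under the larger assumed deficit with SD 15 the responder comparison would reveal the worse arm with power 0.92. The defect is one of order and hierarchy.

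A reader might also infer that a misleading success is close to certain. It is not. With the smaller deficit, the paired test itself is significant in only 70% to 84% of trials, and the contradictory pair of results occurs in 19% to 42%.

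A third tempting step is to replace the endpoint by a continuous between-arm ANCOVA. The Abstract does speak of change in peak oxygen uptake, but Sections 8 and 9.1 and Table 3 define a 10% responder outcome. Changing it would require new outcome definitions and a new sample-size basis, and the present defect does not require it.

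What the defence does not remove is that the test named first for the primary endpoint answers another question and that no rule subordinates it. This is stated text, not detail deferred to an analysis plan.

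**Conclusion.** The point holds as a fault of order and decision rule. As written, the lead analysis of the primary endpoint has no arm term, tests zero change instead of the 10% threshold, and can be significant while telerehabilitation is significantly worse. The chance of that combination is about 19% to 42% under a modest assumed deficit and about 61% to 97% under a larger one. These probabilities rest on assumed gains, SDs and a 100:100 split, so they illustrate the risk and do not predict it. The mismatch between the paired test and the comparative objective needs no assumption: it follows from the text. It should be corrected before the results are analysed.

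**What to change.** In Section 9.1, name one primary analysis: the between-arm comparison of the 10% responder endpoint, by the logistic model already planned. Include arm, baseline peak VO2, and either prespecified confounders or the propensity score mentioned in Section 2, in place of covariates chosen from baseline tests. Analyse patients by the modality in which they started, because Section 5 provides that "Patients in the telerehabilitation group experiencing clinical or technical issues may transition to in-person sessions to ensure therapeutic continuity". Label the paired t-test and Wilcoxon results as descriptive within-arm summaries that cannot establish the primary result. A between-arm ANCOVA of 8-week peak VO2 may be added as supportive.

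The section must also be aligned with the non-inferiority hypothesis in the Abstract. If that is the hypothesis, a margin has to be stated and the interval level (90% in Section 9.1) reconciled with the two-sided 0.05 rule in Section 9.2.

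The change needs revised wording and no new data. The cost is that a likely before-after result no longer counts as the primary result, and that the sponsor must commit to one hypothesis.

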## 2. Methods

### Study Design and Population

The TELEREHAB-HF study is a single-center, prospective, observational, non-pharmacological cohort trial designed to evaluate the clinical efficacy of a home-based, supervised cardiac telerehabilitation program in patients with CHF. The trial will be conducted at the tertiary care center Azienda Ospedaliera Universitaria (AOU) “San Giovanni di Dio e Ruggi d’Aragona” in Salerno, Italy, in collaboration with the University of Salerno. The study aims to enroll 220 adult patients (≥18 years) with a confirmed diagnosis of CHF—classified as heart failure with reduced ejection fraction (HFrEF), heart failure with mildly reduced ejection fraction (HFmrEF), or heart failure with preserved ejection fraction (HFpEF)—and functional class I to III according to the New York Heart Association (NYHA) classification. All participants must be clinically stable and on optimized medical therapy for at least one month prior to enrollment (Figure 1).

Participants will be allocated to the telerehabilitation or standard rehabilitation arm based on patient preference and logistical eligibility (e.g., home safety, access to digital devices, internet connectivity). Although this approach does not involve randomization, both groups will be enrolled under identical inclusion and exclusion criteria. To mitigate potential selection bias, comprehensive baseline characterization and statistical adjustment (e.g., propensity score methods) will be applied. Patients in the intervention group (TELEREHABILITATION-YES) will undergo an 8-week individualized cardiac rehabilitation program performed at home, supported by the Khymeia Virtual Reality Rehabilitation System (VRRS). The program includes real-time video-supervised sessions with a physiotherapist, and continuous monitoring through medical-grade wearable sensors that collect electrocardiogram (ECG), heart rate (HR), peripheral oxygen saturation (SpO_2_), and blood pressure (BP) data. The system also records exercise performance using inertial movement sensors, and all data are transmitted securely to a central digital platform for remote clinical oversight and feedback.

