Additionally, anthropometric measurements—body weight, height, and body mass index (BMI)—will be recorded at each timepoint to monitor weight dynamics, which are clinically relevant indicators of fluid retention and potential decompensation in patients with heart failure [2,28].

Patients with NYHA class IV symptoms, severe renal impairment—defined as an estimated glomerular filtration rate (eGFR) < 30 mL/min/1.73 m^2^—terminal illness, pregnancy, inability to perform physical training, or insufficient digital literacy (in the absence of caregiver support) will be excluded (Table 1).

All clinical, instrumental, and biochemical data will be recorded in anonymized case report forms and stored in a secure, encrypted digital database. The study protocol complies with the Declaration of Helsinki and Good Clinical Practice (GCP) guidelines and has been approved by the Campania 2 Regional Ethics Committee (Approval Number: 14718 of 06.06.2024). The trial is registered at ClinicalTrials.gov under the identifier NCT07023536.

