## 3. Groups and Interventions

Participants enrolled in the study will be allocated to one of two groups based on their voluntary acceptance of the telerehabilitation modality:1.TELEREHABILITATION—YES (Remote Group)2.TELEREHABILITATION—NO (In-Person Group)

Both groups will undergo an 8-week individualized CR program based on international guidelines for heart failure rehabilitation [29]. The intervention includes a combined training protocol delivered 5 times per week for the first 4 weeks, and 3 times per week for the subsequent 4 weeks. Each session lasts approximately 60 min and is structured as follows (Table 2):10 min of interval training (warm-up) including flexibility, breathing, and coordination exercises;40 min of endurance training using a stationary bicycle, aiming at 70% of VO_2_ peak (as determined by baseline CPET) or 75–80% of maximum HR if CPET is not available [30,31,32,33,34];10 min of cool-down exercises with stretching and breathing techniques.

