## 12. Study Limitations and Future Directions

This study has several limitations that should be acknowledged. First, the single-center design may limit the generalizability of findings, as patients are recruited from a single university hospital with specific technological infrastructure and clinical pathways. Future multicenter trials are needed to validate the model in more diverse healthcare settings and populations.

Second, the study does not employ randomized allocation to intervention and control groups, which introduces the potential for selection bias. Although careful matching and baseline characterization are planned to mitigate this issue, a randomized controlled trial would offer a higher level of evidence and should be considered in future research phases. Nevertheless, this pragmatic allocation strategy is particularly relevant in the context of the Salerno province, which includes geographically complex and low-accessibility areas such as the Amalfi Coast and inland Cilento. These regions are often underserved in terms of rehabilitation services. By allowing patients to choose their rehabilitation modality, the protocol increases accessibility and adherence, reflecting the real-world feasibility of implementing home-based telerehabilitation programs in underserved or hard-to-reach populations.

Third, the duration of follow-up (24 weeks), while longer than many previous CTR studies, remains insufficient to evaluate long-term outcomes such as rehospitalizations, cardiovascular events, or mortality. Extended follow-up studies will be necessary to assess the sustained impact and safety of the intervention over time.

Fourth, although the study includes multidimensional clinical and biological assessments, it does not incorporate a formal cost-effectiveness analysis, which is crucial for informing health policy decisions and large-scale implementation. The economic sustainability of the proposed model should be evaluated in subsequent studies.

Fifth, while body weight, height, and BMI are routinely collected and monitored throughout the study, more advanced measures of body composition—such as visceral adiposity—are not included. Considering that fluctuations in body weight are a recognized predictor of heart failure decompensation, this parameter remains clinically relevant and will be carefully analyzed, although the lack of imaging-based adiposity assessment represents a limitation.

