**Figure 5 healthcare-13-02074-f005:**
[figure not shown]
Emergency management flowchart within a tele-rehabilitation program for clinically stable CHF patients. Abbreviations: BNP: B-type Natriuretic Peptide, BP: Blood Pressure, CHF: Chronic Heart Failure, CPET: Cardiopulmonary Exercise Testing, EMS/118: Emergency Medical Services (Italian emergency number 118), HR: Heart Rate, KCCQ-12: Kansas City Cardiomyopathy Questionnaire (12 items), NYHA: New York Heart Association, RPE: Rating of Perceived Exertion, SF-36: Short Form Health Survey (36 items), SpO**_2_**: Peripheral Oxygen Saturation, VO**_2_**max: Maximal Oxygen Uptake, 6MWT: Six-Minute Walk Test.

**Table 1 healthcare-13-02074-t001:** Inclusion and Exclusion Criteria.

Inclusion Criteria	Exclusion Criteria
Age ≥ 18 years	Age < 18 years
Confirmed diagnosis of CHF (HFrEF, HFmrEF, or HFpEF) NYHA functional class I–III	NYHA class IV
Clinically stable for ≥1 month On optimized medical therapy for ≥1 month	Terminal illness with life expectancy < 6 months Anticipated heart transplantation or VAD within 6 months Severe renal dysfunction (eGFR < 30 mL/min/1.73 m^2^)
Able to perform physical exercise	Inability to perform exercise due to medical conditions
Able to provide written informed consent	Severe cognitive impairment (e.g., advanced dementia)
Basic digital literacy (patient or caregiver, for tele-group)	No digital literacy and no caregiver (for tele-group)
Referred to cardiac rehabilitation	Participation in another clinical trial interfering with outcomes
—	Pregnancy or breastfeeding

Abbreviations: CHF: chronic heart failure, eGFR: estimated glomerular filtration rate, HFmrEF: heart failure with mildly reduced ejection fraction, HFpEF: heart failure with preserved ejection fraction, HFrEF: heart failure with reduced ejection fraction, NYHA: New York Heart Association, VAD: ventricular assist device.

**Table 2 healthcare-13-02074-t002:** Comparison of Exercise Components Between Groups.

Exercise Component	TELEREHABILITATION—YES (Remote)	TELEREHABILITATION—NO (In-Person)
Warm-up (10 min)	- 3 min marching in place - 3 min cross-pattern exercises - 1 min sit-to-stand - 3 min breathing with Khymeia spirometer	- 3 min marching in place - 3 min cross-pattern exercises - 1 min sit-to-stand - 3 min breathing with volumetric incentive spirometer
Endurance Training (40 min)	stationary cycling	stationary cycling

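### Section 9.1 selects confounders by baseline significance tests in a non-randomised comparison, omits the propensity and matching methods promised elsewhere, and sits beside contradictory eligibility rules

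*Protocol article*

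**What the plan says.** **Allocation.** Section 2 (Study Design and Population) assigns patients "based on patient preference and logistical eligibility (e.g., home safety, access to digital devices, internet connectivity"). Section 3 describes allocation as "based on their voluntary acceptance of the telerehabilitation modality" and does not mention logistics. Section 12 acknowledges that selection bias is possible.

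**Adjustment.** Three descriptions appear:
- Section 2: "comprehensive baseline characterization and statistical adjustment (e.g., propensity score methods) will be applied".
- Section 12: "Although careful matching and baseline characterization are planned to mitigate this issue".
- Section 9.1, for the logistic model of the ≥10% VO2max response: "The model will be adjusted for clinically relevant covariates identified through baseline comparisons using ANOVA or chi-square tests".

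Section 9.1 mentions neither propensity scores nor matching. It reports odds ratios with 90% confidence intervals.

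**Eligibility.** Section 2 states that "both groups will be enrolled under identical inclusion and exclusion criteria". Later in the same section, patients with terminal illness, pregnancy and so on "or insufficient digital literacy (in the absence of caregiver support) will be excluded", with no restriction to one arm. Section 7 makes caregiver support a requirement for inclusion when digital literacy is limited. Table 1 ties the digital criteria to one arm only, for example "No digital literacy and no caregiver (for tele-group").

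**The concern.** Without randomisation, the between-arm odds ratio is only as credible as the control of confounding. A significance test at baseline answers a different question. Whether a variable passes depends on the number of patients and the size of the imbalance, and takes no account of how strongly the variable predicts the outcome. A strong predictor with a modest imbalance is likely to be dropped, and an irrelevant variable with a chance imbalance is kept. The abstract's hypothesis is non-inferiority, so residual bias towards the remote arm, if it ran that way, would make a favourable conclusion easier to reach.

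The second issue is who the controls are. If the in-person arm includes patients who could not have been assigned to the remote arm, the two arms do not describe the same population. The article leaves it unclear how far this is so.

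**Working it through.** **Inputs.** Section 9.3 gives 200 evaluable patients. Its derivation cannot be reproduced because no SD or response rate is given, but this point does not depend on it. The following are assumptions, because the article does not state them: 100 per arm, a screen at p<0.05, and the confounder strengths below.

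**Step 1: how often the screen finds a real imbalance.** For a standardised difference d with n per arm, the chance of p<0.05 is approximately Φ(d·√(n/2) − 1.96).
- d = 0.2, n = 100: 0.2 × √50 = 1.414; 1.414 − 1.96 = −0.546; Φ = 0.29. Missed: 71%.
- d = 0.3: 0.3 × √50 = 2.121; 2.121 − 1.96 = 0.161; Φ = 0.56. Missed: 44%.
- With a 3:1 split of the same 200 patients (150 and 50), d = 0.2 is found 23% of the time.

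**Step 2: what this does to the odds ratio.** Simulated logistic regressions, 100 per arm, true treatment OR = 1. Unless noted, each confounder has a 0.2 SD imbalance and an outcome OR of 1.5 per SD.

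| Scenario | Screened OR | False positives (nominal 5%) |
|---|---|---|
| One confounder (0.1 to 0.4 SD, OR 1.5 or 2) | 1.01 to 1.05 | 5 to 7% |
| Five, three favouring one arm and two the other | 1.04 | 4.1% |
| Five, correlated | 1.04 to 1.07 | 5 to 6% |
| Five independent, same direction, screen at p<0.20 | 1.07 | 5.3% |
| Three independent, same direction | 1.12 to 1.13 | 6.6 to 6.7% |
| Four independent, same direction | 1.15 | 7.8% |
| Five independent, same direction | 1.19 to 1.20 | 9% |

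Adjusting for all the confounders gives an OR of about 1.00 and false positives of about 5% throughout. In the last row the unadjusted OR is 1.44, so the screen removes more than half of the crude bias but not all of it. Because 9.1 reports 90% intervals, the lower limit is also relevant: in that row it wrongly exceeds 1 in 13.5% of runs with screening, against 4.7% with full adjustment. Raising the outcome OR to 2 per SD with four confounders gives 1.22 and 10.9%.

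**Step 3: eligibility, side by side.** Section 2 says the criteria are identical and excludes digitally unable patients without a caregiver from the study. Section 7 points the same way, although it is written about the remote programme. Table 1 applies the criterion to the remote group only. These cannot all hold.

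A separate route does not depend on that contradiction. Section 2 also allocates on home safety, devices and internet access. A patient who lacks these can only be a control, so the probability of remote allocation is zero. The article does not say how many such patients are expected, so no size can be attached.

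**The case against.** Four objections deserve weight.

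1. *The rule is not a pure p-value screen.* Section 9.1 requires covariates to be clinically relevant, and Sections 2 and 12 commit to further adjustment. The detailed covariate list and balance metric may properly sit in an analysis plan that is not shown. This is fair, and the absence of a list is not the point. The point is that 9.1 states how covariates are identified, the stated route is unsound, and it does not match the other two sections.

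2. *The larger figures need an unfavourable set-up.* They need several independent confounders all favouring one arm. Measures such as peak VO2, 6MWT, SPPB and NYHA class are likely to be correlated, and then the bias is small. This stands, and it is why a range is given.

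3. *A reader might infer that controls who could never go remote make the comparison irreparable.* That is too strong. An average effect over all patients does need everyone to have some chance of either arm. An effect in the telerehabilitation patients needs only that each of them could have been a control, and matching can then leave ineligible controls unmatched.

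4. *Long covariate lists have a cost.* With about 200 patients and an unknown number of responders, many terms could strain a logistic model. This stands and shapes the fix.

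**Conclusion.** The point holds as a risk of residual confounding of unknown size and direction, created by a stated rule that is unsound for this design. Under the assumed 100 per arm and p<0.05 screen, a 0.2 SD imbalance is missed 71% of the time. The resulting odds ratio under no effect runs from about 1.04 (one confounder, or mixed directions) through about 1.07 (correlated confounders, or a looser screen) to about 1.2 with 9% false positives in the upper scenario. Prespecified adjustment removes the part due to measured confounders.

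Two stronger readings are tempting but unsupported. One is that the comparison is certain to stay biased in favour of telerehabilitation: nothing in the article says that digitally or logistically excluded controls would respond worse on a relative VO2max gain, and Section 12 names access from remote areas as another driver of choice. The other is that the in-person arm definitely admits digitally excluded patients: that takes Table 1's side of a contradiction which Sections 2 and 7 put the other way. What is established is the inconsistency, plus possible non-overlap through home, device and internet eligibility.

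**What to change.** - In 9.1, delete the selection of covariates by baseline tests. Adjust for a short prespecified list of variables related to prognosis or to choice of modality and already collected, such as baseline peak VO2, age, NYHA class, HF phenotype or LVEF, NT-proBNP and 6MWT. Keep the list to what the expected number of responders can support, or summarise it in a propensity score.
- Carry the promised propensity method into 9.1, judge balance by standardised differences, and make Sections 2, 9.1 and 12 name the same method.
- Reconcile Sections 2, 3 and 7 and Table 1 on how patients are allocated and whether the digital criterion applies to both arms.
- Record remote eligibility (home, device, internet, digital support) for every patient. Compare the arms among patients eligible for both modalities, at least as a prespecified sensitivity analysis.

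The cost is revised wording and one screening item for controls. Intervals will be slightly wider, and a few controls drop out of the restricted comparison. Data collection is under way, so eligibility should be recorded now and the list fixed before outcomes are examined.
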